#### Screening questionnaire

The Pediatric Emotional Distress Scale-Early Screener (PEDS-ES [28]) is a 21-item caregiver report questionnaire designed to be used to screen for elevated trauma-related behaviour in children aged 2–10 years. Caregivers are required to rate the frequency at which the behaviour has occurred since the trauma on a 4-point Likert scale (0 equal or less often, 1 = a little more often, 2 = much more often, and 3 = very much more often). The PEDS-ES has demonstrated promise as a screening tool for identifying young children (aged 2–6 years) who are at risk of developing PTSD following accidental injury [28]. A score ≥8 indicates that a child is in the at-risk range for developing PTSD.

#### Primary clinical outcomes

The primary clinical outcome, reduction in PTSS severity scores, will be assessed using the Diagnostic Infant and Preschool Assessment (DIPA). The DIPA [29] is a semi-structured diagnostic interview conducted with the primary caregiver of children aged 1–6 years. The DIPA has demonstrated acceptable test-retest reliability [29]. The PTSD module of the DIPA will be used to assess total PTSS severity and impairment in the child.

#### Secondary clinical outcomes

The PTSD module of the DIPA will be used to provide a PTSD diagnosis. The Young Child PTSD Checklist [30] is a 42-item parent-report questionnaire that assesses criteria of the *Diagnostic and Statistical Manual of Mental Disorders, Fifth Edition* (DSM-5), for PTSD in young children. It will also be used to provide a measure of PTSS severity scores and impairment in the child.

The Child Behavior Checklist for ages 1.5–5 years (CBCL/1.5-5; [31]) will be used to assess for changes between the intervention and control groups in total problem behaviour scores and internalising and externalising difficulties. The CBCL/1.5-5 is a 100-item parent-report checklist that measures emotional and behavioural functioning in children ages 1.5–5 years of age. The CBCL/1.5-5 has demonstrated good psychometric properties [31].

The Posttraumatic Diagnostic Scale (PDS; [32]) is a 49-item self-report questionnaire that is used to screen and assess for PTSD in adults. Psychometric evaluation has demonstrated acceptable to excellent internal consistency, good test-retest reliability and acceptable convergent and concurrent validity [33]. The DSM-5 version of the PDS will be used in this study to provide a measure of PTSD symptom severity ratings and level of impairment in functioning among the parents.

#### Additional outcomes

Demographic information (e.g., child and parent ages, socio-economic status, family structure), will be obtained by using questions included in the questionnaire booklet completed at the time of screening. Injury- and hospital-related information (e.g., injury severity, length of stay in hospital) will be obtained from the child’s medical record. The feasibility and acceptability of the intervention will be assessed by looking at (1) participant approach and consent rates, (2) treatment completion, (3) attrition rates, (4) parent satisfaction with the intervention and (5) therapist feedback.

### Sample size

Published data for a sample of 32 high-risk preschool children (had PTSD 1 month post-burn) who received TAU indicate that their PTSS decreased by an average of three symptoms (from 7 [SD = 2.1] to 4 [SD = 3.3]) over 6 months [3]. We assume that, over the course of 6 months, the number of symptoms in participants in the CARE group will have a mean reduction of five (SD = 3) and the number of symptoms in participants in the TAU groups will have a mean reduction of three (SD = 3). These data are based on the level reported in the recovered high-risk children (i.e., those who no longer met PTSD diagnostic criteria at 6 months) [3]. Consequently, we anticipate the mean difference in the number of symptoms between the CARE and TAU groups at 6 months will be two. We assume the SD will be 3 symptoms and an α-level of 0.05. Using a two-sided test, a total sample size of 56 children (28 in each treatment group) is required to complete the study with a power of 80 %. This is equivalent to an effect size of 0.75. We anticipate that approximately 25 % of participants will not complete the 6-month interviews; therefore, we will randomise 76 individual children to get complete primary outcome data for 56 participants.

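### A difference of 2 symptoms with SD 3 is an effect size of 0.67, not 0.75, so 28 children per arm give about 69% power, not 80%.

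*Protocol article*

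**What the plan says.** All the inputs are in one paragraph of the protocol article, under Sample size.

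- **Difference.** Mean reductions over 6 months of 5 symptoms with CARE and 3 with TAU, so that "the mean difference in the number of symptoms between the CARE and TAU groups at 6 months will be two".
- **SD and alpha.** Each mean reduction carries an SD of 3. The paragraph then repeats: "We assume the SD will be 3 symptoms and an α-level of 0.05".
- **Sidedness.** "Using a two-sided test".
- **Result.** "a total sample size of 56 children (28 in each treatment group) is required to complete the study", with power of 80%.
- **Effect size.** "This is equivalent to an effect size of 0.75".
- **Attrition.** About 25% loss by 6 months, hence 76 randomised to retain 56.

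The Statistical analysis plan section of the same article specifies a linear regression of 6-month change on treatment group, with the baseline score as a covariate. The Sample size section gives no baseline-to-follow-up correlation and claims no gain in precision from that adjustment.

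**The concern.** The standardised effect is fixed by two numbers that the section states outright, 2 and 3. Their ratio is 0.667, yet the section reports 0.75, and the sample size of 28 per arm fits 0.75. Rounding does not explain the gap. The SD of 3 appears three times, and the difference of 2 is both stated and obtainable as 5 − 3.

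This paragraph is the only justification for the size of the primary comparison. If the power is really about 69%, the chance of missing the planned effect is nearly one in three. A non-significant result could then be taken as evidence from an adequately powered trial, when on the trial's own assumptions it is not. The Background itself lists an a priori power analysis among the marks of a sound trial in this field.

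**Working it through.** **Inputs (all from Sample size).** Difference Δ = 5 − 3 = 2; SD σ = 3 in both arms; two-sided α = 0.05; power 0.80; 1:1 allocation; 28 completers per arm; 25% loss.

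**1. Which inputs give the plan's figure?** With n per arm = 2(z₁₋α/₂ + z₁₋β)² / d² and z-values 1.960 and 0.842:

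- d = 0.75: 2 × (2.802)² / 0.5625 = 27.9, so 28 per arm. Power at 28 per arm is 0.801 (normal) or 0.787 (noncentral t).

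So 28 follows from d = 0.75. With Δ = 2 that needs σ = 2 / 0.75 = 2.67; with σ = 3 it needs Δ = 0.75 × 3 = 2.25. The section states neither.

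**2. What do the stated inputs give?** d = 2/3 = 0.667.

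| Quantity | Normal approximation | t-test |
|---|---|---|
| n per arm for 80% power | 35.3, so 36 | 36.3, so 37 |
| Completers in total | 72 | 74 |
| Power at 28 per arm | 0.703 | 0.688 |
| Detectable d at 28 per arm, 80% power | 0.749 | 0.762 |

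Normal power at 28 per arm: d√(n/2) = 0.667 × √14 = 2.494; 2.494 − 1.960 = 0.534; Φ(0.534) = 0.703. The detectable difference by the t-test is 0.762 × 3 = 2.29 symptoms. The type II error is 1 − 0.688 = 0.31.

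**3. One-sided variant.** With d = 0.667 and a one-sided 5% test, the normal formula gives 28 per arm (power 0.802; t-test 0.793). This also reproduces 28, but it contradicts the stated two-sided test and leaves 0.75 unexplained as the ratio of 2 to 3.

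**4. Baseline-adjusted variant.** The section quotes published SDs of 2.1 at the start and 3.3 at 6 months. Combined with a change SD of 3:

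- r = (2.1² + 3.3² − 3²) / (2 × 2.1 × 3.3) = 6.30 / 13.86 = 0.4545
- residual SD = 3.3 × √(1 − 0.4545²) = 2.94
- d = 2 / 2.94 = 0.680; power at 28 per arm = 0.706 (t) or 0.721 (normal)

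To bring the residual SD down to 2.67 from a follow-up SD of 3.3 needs r = √(1 − (2.67/3.3)²) ≈ 0.59. With SDs of 2.1 and 3.3, that correlation implies a change SD of √(4.41 + 10.89 − 2 × 0.59 × 6.93) ≈ 2.67, which is no longer the stated 3.

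**5. Attrition step.** 56 / 0.75 = 74.7, so 75, or 76 in whole blocks of four. This step is sound. The same rule applied to 72 or 74 completers gives 96 or 99 randomised (96 or 100 in whole blocks of four).

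**The case against.** The strongest reply is that the planned analysis adjusts for baseline and so may have more power than an unadjusted t-test. The sentence giving the SD of 3 directly follows the one about the difference at 6 months, so it could be read as the SD of the 6-month score. On that reading a baseline correlation of about 0.46 gives a residual SD of 2.67, d = 0.75 and t-test power of 0.787; a correlation of 0.50 gives 0.808. This is possible, and the calculation in step 4 depends on taking 3 as the SD of change. But the section attaches the SD of 3 to the mean reductions and states no correlation, so this explanation would have to be supplied from outside the text.

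Second, 76 are to be randomised. If all were retained (38 per arm), power at d = 0.667 would be about 0.82 to 0.83. Repeated-measures models or imputation could also use some partial data. The claim at issue, however, is that 56 completers suffice, and the plan expects to lose the other 20.

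Third, the origin of 28 cannot be settled: it fits d = 0.75 two-sided and also d = 0.667 one-sided. That stands, and it is a reason to include sidedness in the correction.

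Fourth, the error does not bias the treatment estimate, its confidence interval or the type I error. That also stands. It concerns what the trial can claim about its sensitivity, not the validity of its estimate.

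**Conclusion.** The concern holds. On the stated difference of 2, SD of 3 and two-sided 5% test, the effect size is 0.667. The planned 56 completers then give about 69% power (70% by the normal approximation). Power of 80% needs 72 to 74 completers, or else a true difference of about 2.29 symptoms. These figures assume an unadjusted two-sample comparison with exactly 28 completers per arm. Baseline adjustment raises power only to about 71% on the section's own SDs if 3 is the SD of change. It would reach about 80% only under an SD reading and a correlation that the section does not state. The article describes two separate trials and no pooled analysis that could make up the shortfall. Because this is a stated property of the primary comparison and is cheap to correct, it should be corrected.

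**What to change.** Rewrite the Sample size paragraph so that difference, SD, effect size, sidedness, power and number agree. Any one of these would do, without changing enrolment:

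1. State the effect size as 0.67 and the power as about 69% for 56 completers, two-sided.
2. Keep 80% power and state that the detectable difference with 28 per arm is about 2.3 symptoms (d about 0.76).
3. If 0.75 was meant to reflect baseline adjustment, state the residual SD of 2.67, the correlation it needs (about 0.59 with a follow-up SD of 3.3, or about 0.46 with a follow-up SD of 3), and the support for that value.

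In each case, confirm that the calculation was two-sided. The cost is one reworded paragraph, plus any other trial text that repeats the figure, and under option 1 a less favourable stated power. Keeping 80% power for a difference of 2 with SD 3 would instead require about 96 to 100 randomised at 25% loss, against the planned 76. An accurate statement of the present design does not require that.

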### Randomisation

A computerised random number generator (https://www.sealedenvelope.com/simple-randomiser/v1/lists) was employed by a researcher not involved in the study to create a randomisation list using blocks of four study participants. Third-party concealment of group allocation was ensured by using a numbered series of opaque, sealed envelopes prepared in advance. Following the baseline assessment, the interviewer opens the sealed envelope to reveal assignment of the participant to the CARE intervention or to TAU.

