## Methods/design

### Design and procedures

The study design for the two proposed research studies is a two-arm, parallel-group superiority prospective RCT comparing the CARE intervention with TAU. The Consolidated Standards of Reporting Trials (CONSORT) guidelines for RCTs will be followed, and the study protocol also adheres to the Standard Protocol Items: Recommendations for Interventional Trials (SPIRIT 2013) (see checklist in Additional file 1). The study involves five stages (see Fig. 1). Stage 1 participant recruitment, will consist of the research team identifying and inviting eligible families to participate in the study and obtaining informed parental consent when the child first presents to hospital. In stage 2, screening, participating parents will be contacted approximately 6–8 days post-accident to complete the screen. Stage 3, baseline assessment and randomisation, will involve the completion of baseline measures by parents of children identified as at risk of PTSD approximately 1–3 days post-screen. Immediately following undergoing baseline assessment, families will be randomly assigned to either (1) the CARE intervention group or (2) TAU. Stage 4, intervention, commences following randomisation. Stage 5, follow-up assessment, consists of 3- and 6-month assessments conducted by trained psychologists blinded to treatment allocation.

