### Setting

One RCT is being conducted in Australia at the Lady Cilento Children’s Hospital (LCCH), Brisbane, and the other in Switzerland at the University Children’s Hospital, Zurich.

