### Blinding

Randomisation occurs after the baseline assessment; therefore, all interviewers are blinded to treatment condition during the interview. The 3- and 6-month outcome assessments are completed by different psychologists who are blinded to the treatment condition.

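### With one block size of four and the baseline interviewer opening the envelopes, up to one third of allocations could be deduced, so baseline blinding is not secured

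*Protocol article*

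**What the plan says.** The Randomisation section states a single block size: a researcher outside the study used a computer generator to "create a randomisation list using blocks of four study participants". No varying sizes and no stratification are mentioned. On concealment it says: "Third-party concealment of group allocation was ensured by using a numbered series of opaque, sealed envelopes prepared in advance". On who learns the result: "Following the baseline assessment, the interviewer opens the sealed envelope to reveal assignment of the participant to the CARE intervention or to TAU".

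The Blinding section then reasons: "Randomisation occurs after the baseline assessment; therefore, all interviewers are blinded to treatment condition during the interview". For follow-up it adds: "The 3- and 6-month outcome assessments are completed by different psychologists who are blinded to the treatment condition".

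Four other places bear on the point. Setting gives one hospital per trial. Primary clinical outcomes describes the Diagnostic Infant and Preschool Assessment (DIPA) as a semi-structured interview with the caregiver. Measures places the baseline assessment at about 9–11 days after injury. The Statistical analysis plan section makes change over 6 months the main outcome, with the baseline score of the same measure as covariate.

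**The concern.** Randomising after the baseline interview keeps the current envelope sealed. It does not stop an interviewer from working out its content from the envelopes already opened in the same block. Here the role that accumulates that information is the role that conducts the next baseline interview. The outside researcher's part ends with making the list, so third-party preparation does not close this route.

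Two things could be affected. The first is scoring: a semi-structured interview leaves room for judgement, and the resulting score adjusts the primary comparison. The second is timing: if two children fall due in the same few days, the order in which they are interviewed decides which child receives a foreseeable envelope.

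**Working it through.** **Inputs.** Block size 4, two arms and one hospital per trial (Randomisation, Design and procedures, Setting); 1:1 allocation, implied by 28 per group; 76 randomised, 25% loss, SDs 2.1, 3.3 and 3, and target difference 2 (Sample size).

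**The plan's own figure.** The article gives no predictability figure. The base number reproduces closely: 56/(1 − 0.25) = 74.7, so 75, against the stated 76. And 76/4 = 19 whole blocks. The article does not say whether 76 is per trial or for both; the shares below hold either way.

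**Certain allocations, one fully informed interviewer.** A block has 6 equally likely orders. An allocation is certain once one arm is used up in its block.
- Positions 1 and 2: never certain.
- Position 3: certain if the first two agree, probability 2/6 = 1/3.
- Position 4: always certain.

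Mean share = (0 + 0 + 1/3 + 1)/4 = 1/3. Over 76 children, 76/3 = 25.3.

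**Best guess.** The chances of being right by position are 1/2, 2/3, (1/3)(1) + (2/3)(1/2) = 2/3, and 1. The mean is (17/6)/4 = 0.708, against 0.50 for a guess with no information.

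**Several interviewers, no sharing.** Suppose each of m interviewers sees only their own envelopes and cases fall to them at random. Certainty then needs the two earlier same-arm envelopes both to have been opened by the present interviewer, probability 1/m². The share is 1/(3m²).

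| Interviewers | Certain share | Of 76 |
|---|---|---|
| 1, or full sharing | 33.3% | 25.3 |
| 2 | 8.3% | 6.3 |
| 3 | 3.7% | 2.8 |

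**Varying block sizes.** In a simulation of lists of 76, with the candidate sizes known but not their order, a fully informed observer is certain of about 5% for sizes 4 and 6, about 4% for 2, 4 and 6, and about 2% for 4, 6 and 8. Fixed blocks of 6 or 8, if known, still leave 25% or 20%.

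**What it could do to the estimate (illustration; the mis-scoring is assumed).** With baseline as covariate, the bias is the baseline slope times the artificial baseline gap between arms. If the three SDs in Sample size are treated as one sample, the covariance is (2.1² + 3.3² − 3²)/2 = (4.41 + 10.89 − 9)/2 = 3.15, and the slope is 3.15/4.41 = 0.71.
- Each predictable CARE child scored one symptom too high: gap 1/3, bias 0.71 × 0.33 = 0.24 symptoms.
- CARE one too high and TAU one too low: gap 2/3, bias 0.71 × 0.67 = 0.48. Slopes of 0.3 to 0.7 give 0.20 to 0.47.
- Two non-sharing interviewers: gaps 1/12 and 1/6, bias 0.06 and 0.12.

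The planned difference is 2 symptoms. A higher baseline in CARE would favour CARE.

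**Would the planned balance check show it?** It acts at p < 0.001. With SD 2.1 and 38 per arm, the standard error is 2.1 × √(2/38) = 0.48. The threshold is about 3.29 × 0.48 = 1.6 symptoms, well above a gap of 0.67.

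**The case against.** A third-party list in numbered, opaque, sealed envelopes, opened after baseline, is a recognised concealment method. The one-third figure is a maximum: it needs an interviewer who knows the block size, the position in the block and every earlier allocation in it. The article does not say that interviewers were told the block size, and it speaks of interviewers in the plural. Consent at first presentation and a caregiver-completed screen with a cut-off of 8 both precede baseline, which limits selective enrolment. The outcome ratings come from different, blinded psychologists.

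All of this stands, and it bounds the size. Using change as the outcome adds no second source of bias either: with baseline as covariate, regressing change or the final score gives the same treatment coefficient.

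Publication of the block size is also a weak argument for most of the sample. The article is dated 28 July 2016; recruitment began on 1 April and 3 June 2014 and was expected to end with 2016. Taking 31 December 2016 as the end, 849/1005 = 84% and 786/942 = 83% of the recruitment periods had passed. On even accrual (an assumption), about 12 of 76 envelopes were still unopened. For those, however, the block size was in print.

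What the objection does not rescue is the inference in the Blinding section, which presents blinding of all interviewers as a consequence of timing alone.

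**Conclusion.** Baseline blinding is not secured by the procedure described. At most one third of allocations, about 25 of 76, could be deduced before or during the baseline DIPA by an interviewer who knows the block size and tracks every envelope. The share is about 8% with two interviewers who do not share allocations and about 4% with three. The exposure is confined to baseline scoring and interview timing, and so to the covariate in the primary analysis. Under deliberately unfavourable scoring assumptions the bias stays below half a symptom, against a planned difference of 2.

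A reader might infer that one third of allocations were in fact known, that concealment failed, or that the treatment comparison is biased. The documents support none of these. They do not say what interviewers knew, how many there were or whether they shared allocations, and they give no sign of mis-scoring.

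**What to change.** 1. For envelopes not yet used, have the independent researcher reissue the list with randomly varying block sizes, for example 2, 4 and 6, not disclosed to site staff.
2. Have existing staff other than the baseline interviewer, such as the list holder or the treating psychologist, release the assignment only after the baseline DIPA score is locked. This matters as much as the first step, because any blocking leaves some advantage to someone who sees the sequence.
3. Reword the Blinding sentence to say that the current assignment is concealed during the baseline interview.
4. Compare baseline DIPA scores by arm in predictable positions (the fourth in each block, and the third where the first two agree) against the rest. Treat this as descriptive. With SD 2.1 and about 12.7 predictable and 25.3 other children per arm, the arm gaps have standard errors 2.1 × √(2/12.7) = 0.83 and 2.1 × √(2/25.3) = 0.59, and their difference √(0.83² + 0.59²) = 1.02. Only a large distortion would show.

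The cost is a new list, new envelopes and a small procedural change with existing staff. Final arm imbalance could be slightly larger: at most three if enrolment stops inside a block of six, against two inside a block of four, plus up to two if the change is made mid-block. Steps 3 and 4 remain useful even if few envelopes are left.

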### Blinding

Randomisation occurs after the baseline assessment; therefore, all interviewers are blinded to treatment condition during the interview. The 3- and 6-month outcome assessments are completed by different psychologists who are blinded to the treatment condition.

### Statistical analysis plan

Prior to investigating treatment outcome, the intervention and control groups will be compared for pre-treatment equivalence by using demographic and baseline measures (e.g., sex, age, injury severity, child PTSS, parent PTSS). If significant differences are found (*p* < 0.001), this will be taken into account by including these variables as covariates in outcome analyses. The association between completers and non-completers and baseline characteristics will be investigated using Fisher’s exact test and Student’s *t* tests. The outcome data will be analysed and reported in terms of statistical significance of differences between groups in change over time, adjusting for the value of the outcome at baseline. To test the association between treatment group and outcome, we will do a linear regression, with the main outcome being change over 6 months and the independent variables being treatment group (CARE or TAU), and the baseline score on the outcome under investigation will be included as a co-variable. When appropriate, repeated-measures analyses will be used to compare the two groups with respect to improvement over time. Generalised estimating equations and generalised linear mixed models will be employed. For sensitivity analysis, if any systematic differences are found according to assessment completion, we will re-run analyses using 3- and 6-month outcome data imputed using multiple imputation techniques. Analyses will be conducted on an intention-to-treat basis, with individuals analysed on the basis of the groups to which they were randomised, regardless of the treatment they received. We define statistical significance as *p* < 0.05.

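### Apart from the outcome's own baseline score, covariates enter the models only if a between-arm baseline test gives p < 0.001, so baseline parent PTSS will in practice never be used in the child-outcome models

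*Protocol article*

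**What the plan says.** The Statistical analysis plan section of the protocol article states that "the intervention and control groups will be compared for pre-treatment equivalence by using demographic and baseline measures". The examples it gives are "demographic and baseline measures (e.g., sex, age, injury severity, child PTSS, parent PTSS". The consequence is a rule with a numeric threshold: "If significant differences are found (*p* < 0.001), this will be taken into account", and the way it is taken into account is "this will be taken into account by including these variables as covariates in outcome analyses".

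The same section describes the main regression, in which "the baseline score on the outcome under investigation will be included as a co-variable". No test is attached to that term. Baseline child PTSS is therefore always adjusted for in the primary analysis, and baseline parent PTSS in the parent-outcome analysis. No other covariate is named as unconditional.

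The Randomisation section describes a computer-generated list in blocks of four with sealed envelopes, opened after the baseline assessment. The Background section states that parental distress contributes to how children's trauma symptoms develop and persist, and Table 2 schedules the parent measure (PDS) at the baseline time point.

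**The concern.** When allocation is properly random and concealed, any baseline difference between the arms is chance. A significance test of that difference has a null hypothesis that is true by design, so its p-value does not say whether adjustment is worthwhile. That depends on how strongly the variable predicts the outcome, which the test does not measure.

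The threshold is also so strict that the rule can hardly ever act. It reads as a safeguard against imbalance but delivers almost no adjustment beyond the outcome's own baseline score. This matters most for parent PTSS: the article itself treats parental distress as a driver of child symptoms and collects it at baseline, yet it would essentially never enter the model for child PTSS. At stake are precision in a small trial and moderate chance imbalances that stay in the estimate.

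**Working it through.** **Inputs from the Sample size section.** "we will randomise 76 individual children to get complete primary outcome data for 56 participants", which is 38 per arm at 1:1. "Using a two-sided test, a total sample size of 56 children (28 in each treatment group) is required". It is anticipated that "the mean difference in the number of symptoms between the CARE and TAU groups at 6 months will be two". The assumed SD of change is 3; the cited TAU sample has SD 2.1 at the start and 3.3 at 6 months. From the Statistical analysis plan section: threshold p < 0.001, taken as two-sided because sidedness is not stated.

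**The plan's own figures.** The article gives no figure for the imbalance its rule would detect, so there is none to reproduce. The dropout step does reproduce: 56/0.75 = 74.7, so 75 against the stated 76. The 28 per arm does not follow from difference 2 and SD 3: at two-sided 0.05 and 80% power these give 36 per arm (normal approximation). That is a separate matter, but it explains why the starting power below is under 80%.

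**How large a difference opens the gate.** Smallest standardised difference = t(0.9995, 2n − 2) × √(2/n).

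| n per arm | t | √(2/n) | Difference needed |
|---|---|---|---|
| 38 (randomised) | 3.427 | 0.2294 | 0.79 SD |
| 28 (completers) | 3.480 | 0.2673 | 0.93 SD |

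The article does not say whether 76 applies to each trial or to both together. If to both, with 19 per arm in each trial, the figure is 3.582 × 0.3244 = 1.16 SD. For a binary variable such as sex at 38 per arm, the gap must be about 39 percentage points (for example 15/38 against 30/38, Fisher p = 0.0009).

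**How often it opens.** Under randomisation, 0.1% per variable. For five independent variables, 1 − 0.999⁵ = 0.5%.

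**How often a smaller imbalance arises.** P(|d| > x) = 2 × [1 − Φ(x/√(2/n))]. At 38 per arm:
- x = 0.3: 0.3/0.2294 = 1.31, probability 19%.
- x = 0.5: 0.5/0.2294 = 2.18, probability 3%.

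**Residual SD after adjusting for baseline.** With SDs 2.1 and 3.3 and a change SD of 3, the implied correlation is (2.1² + 3.3² − 3²)/(2 × 2.1 × 3.3) = 6.30/13.86 = 0.45. The residual SD is 3.3 × √(1 − 0.4545²) = 2.94.

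**Shift from an unadjusted imbalance.** Shift = d × r × 2.94, where r is the covariate's partial correlation with the outcome given the baseline score, and d is the imbalance in the part of the covariate that the baseline score does not explain. The documents give no r; 0.3 to 0.5 is an assumption. At d = 0.3:
- r = 0.3: 0.3 × 0.3 × 2.94 = 0.26 symptoms, 13% of 2.
- r = 0.5: 0.3 × 0.5 × 2.94 = 0.44 symptoms, 22% of 2.

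**Power at 28 per arm if such a covariate is always included.** Difference 2, residual SD 2.94 × √(1 − r²), two-sided t-test at 0.05.

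| r | Residual SD | Power |
|---|---|---|
| 0 | 2.94 | 71% |
| 0.3 | 2.80 | 75% |
| 0.4 | 2.69 | 78% |
| 0.5 | 2.55 | 82% |

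**Simulation check.** With 10,000 trials per setting, 28 per arm and a true effect of 2/3 SD, power under the p < 0.001 rule was 68% to 69%; with the covariate always included it was 72% (r = 0.3) and 80% (r = 0.5). The simulation starts lower because it uses the full SD of 3. Type I error was 5.1% to 5.4% under the rule and 5.0% to 5.1% with the covariate always included.

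**The case against.** The strongest defence is that the rule does little harm because it hardly ever acts. The plan then amounts to treatment plus the baseline outcome score, which is a valid analysis of covariance and already contains what is probably the strongest predictor. Type I error stays near 5%. This stands: the issue is efficiency, not validity.

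Three stronger readings are tempting, and the documents do not support them.
- A reader might infer that no covariate enters without passing the test. The baseline score of the outcome under analysis always enters, so an imbalance in baseline child PTSS is adjusted in the primary analysis whatever its p-value.
- A reader might call the unadjusted shift a bias. It is a shift conditional on a chance imbalance; over repeated randomisation the estimate is unbiased, and its confidence interval already reflects that variation.
- A reader might take the 0.79 SD threshold, or a 0.5 SD imbalance, as the typical damage. A 0.5 SD imbalance arises in only about 3% of trials per variable at 38 per arm, and one of 0.79 SD in about 0.1%. The 0.3 SD case is the fairer illustration.

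Two further objections hold in part. The 0.3 to 0.5 range has no source in the article, and at its low end the power gain is about 4 points. The article supports only parental distress as prognostic: it does not say that age or injury severity predicts child PTSS, and it defines no common severity scale for the mixed injuries in the Australian trial. That limits the remedy but does not rescue the rule. A fuller covariate list may sit in an analysis plan not shown, but the threshold is stated here and is open to criticism as it stands.

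**Conclusion.** The point holds for covariates other than the outcome's own baseline score: age, sex, injury severity, and parent PTSS in the child-outcome models. For these, the rule tests a null that randomisation makes true and sets a threshold that is almost never reached, so prognostic information already collected goes unused. The loss is best supported for parent PTSS, because the article itself names parental distress as a contributor to child symptoms.

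The size is moderate. Imbalances of at least 0.3 SD occur in about 19% of trials per variable, and the forgone gain is roughly 4 to 12 percentage points of power at 28 per arm. These figures rest on a two-sided test, 38 randomised and 28 completing per arm within a trial, a residual SD of 2.94 and an assumed partial correlation of 0.3 to 0.5. The statement that the gate almost never opens does not depend on that correlation. The change should be made, but the planned analysis is not invalid without it.

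**What to change.** In the Statistical analysis plan section, delete the between-arm significance tests at baseline and the p < 0.001 rule, and present baseline characteristics by arm descriptively. For the child-outcome models, prespecify the baseline score of the outcome plus the baseline parent PDS score, both included whatever the observed balance. Add child age or injury severity only if the team justifies it as prognostic; injury severity first needs a defined measure that works across the injury types enrolled.

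Keep the comparison of completers with non-completers. It serves a different purpose, since it informs the multiple-imputation sensitivity analysis.

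The cost is a change of wording and one to three degrees of freedom, with no new data. If injury severity is included, its definition must also be written down.
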